## Methods

2

### Research design

2.1

This study is a cohort study with three measurement points conducted at 6- to 12-month intervals (*n* = 600). The impact of the health communication campaign will be evaluated by measuring indicators of knowledge, attitudes and practices related to burn first aid, as well as psychological variables and health information-seeking variables, among the following groups: the exposure group (i.e., burn survivors [*n* = 200] and caregivers [*n* = 100] exposed to campaign messages), the non-exposure group (i.e., burn survivors [*n* = 250] not exposed to campaign messages) and the Photovoice group (i.e., burn survivors [*n* = 50] who participate in Photovoice and are exposed to the campaign messages). Figure 1 presents the campaign process and the planned activities in different phases.

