**Methods and analysis:**

This cohort study will follow 600 participants (*n* = 600; *n* = 500 burn survivors; *n* = 100 caregivers) with three measurement points at 6- to 12-month intervals. The primary outcomes are knowledge, attitudes and practices regarding burn injuries. The secondary outcomes are meaning in life; gratitude, resentment and appreciation; hope; optimism; temporal satisfaction with life; coping strategies; social interaction anxiety; self-stigma and resilience, measured using the Meaning in Life Questionnaire, the Gratitude, Resentment and Appreciation Scale, the Adult Workers Hope Scale, the Patient Optimism Scale, the Temporal Satisfaction with Life Scale, the COPE Inventory, the Social Interaction Anxiety Scale, the Self-Stigma Scale and the Brief Resiliency Scale, respectively. The participants are grouped as follows: the exposure group (i.e., burn survivors [*n* = 200] and caregivers [*n* = 100] exposed to campaign messages), the non-exposure group (i.e., burn survivors [*n* = 250] not exposed to campaign messages) and the Photovoice group (i.e., burn survivors [*n* = 50] who participate in Photovoice and are exposed to the campaign messages). This design evaluates the impact of the health communication campaign and determines whether Photovoice has any additional effects on the primary and secondary outcomes.

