Social media has the potential to play a pivotal role in raising public awareness and providing critical information that can aid prevention, improve mental health and reduce stigma (23–25). Recent campaigns in high-income countries show the feasibility of social media (i.e., Facebook, Instagram and TikTok) as an ideal platform for engaging with a wide range of audiences and for delivering public health messages (24). In LMICs, health communication interventions incorporating mass media communication and visual elements demonstrate improvements in knowledge related to burn safety and first aid (3). Additionally, community-based health education sessions consisting of interactive workshops and consultations with the target communities have been shown to be feasible and acceptable strategies for improving knowledge of first aid and prevention in rural areas in Bangladesh (10, 19). Pakistan is an ideal location to implement a health education campaign incorporating social media, mass media communication and community health education sessions. There were approximately 71 million social media users in Pakistan as of January 2022, equivalent to 31% of the total population (25). Furthermore, evidence from a large-scale randomised control trial (RCT) (*N* = 18,554) evaluating the impact of a health education intervention on heat-related outcomes and literacy demonstrated the feasibility and effectiveness of the intervention. The intervention was found to be effective in reducing hospital visits and enhancing heat literacy when compared to the control group receiving usual care in Pakistan (26).

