The present study is one of the work packages of a larger research programme entitled ‘Burns rehabilitation: A multidisciplinary programme for burns management, treatment and prevention in low-income countries. The project is funded by the National Institute of Research (NIHR) under NIHR Research and Innovation for Global Health Transformation Call 4. The work packages (WPs) of the programme are as follows: understanding the context and intervention co-development (WP1); development and implementation of a national burn registry (WP2); clinical and cost-effectiveness evaluation of the burns care and rehabilitation programme in Pakistan compared to usual care (WP3); development and evaluation of a social media campaign to promote burn prevention and reduce burn-related stigma (WP4); engagement with key informants and policymakers to better understand, prevent and manage burn-related injuries (WP5); and development of sustainable capacity and capability in treatment and rehabilitation for burn injuries and research (WP6). The proposed health education social media campaign, informed by the WP1 findings, will be embedded within WP5 and WP6 to guide policies on burn prevention and management, along with initiatives for capacity and capability building in Pakistan.

The study uses Photovoice to develop and evaluate a collaborative, population-level health education and communication campaign aimed at improving burn prevention and first aid knowledge while reducing burn-related stigma for burn survivors in Pakistan. The campaign will be disseminated through social media platforms to increase its reach and scalability in Pakistan. The present campaign will be the first to evaluate the immediate, medium and long-term effects of the initiative on burn-specific knowledge and on the psychological well-being (meaning, gratitude, life satisfaction, resilience, etc.) of the participants (burn survivors, caregivers, health and emergency care professionals and key informants) in the Photovoice process and subsequent interventions.

The main objectives of this study are as follows:

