#### Procedure

2.2.3

The research team will recruit burn survivors and caregivers from 12 burn centres based in seven project sites across Pakistan to measure existing indicators of knowledge, attitudes and practices on burn prevention, as well as psychological variables, health information-seeking variables and demographics.

Burn survivors and their family members will be invited to fill out online questionnaires (baseline assessment). The research assistants will distribute posters and leaflets at participating centres and waiting rooms, introducing the study and providing the research team’s contact information for further enquiries. The research assistants will also attend the patient and/or family consultations to introduce the study and obtain consent for a follow-up call with the research team. During the follow-up call (within the first 24 or 48 h after the initial contact), the research assistants will ensure that interested burn survivors and their family members understand what their participation entails, and will confirm their willingness to provide informed consent. After informed consent is obtained, burn survivors and their family members will be asked to complete the same questionnaires at 6- to 12-month intervals up to a total of two times throughout the study (see Figure 2 for the CONSORT diagram). If they are literate, as determined during the informed consent process, they will receive a text message with a Qualtrics questionnaire link. If they are illiterate, a research assistant from the research team will call them for the completion of the questionnaires on the phone. Consent for collecting personal information will be obtained during the informed consent process.

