## Data analysis plan

4

To compare changes in self-reported outcomes within groups across two time points (see Table 1) in the sample (*N* = 600), we will implement linear mixed-effects models implemented in R (R version 3.6.1) (51) using the lme4 package and in SAS 9.4. This method considers correlations within participants, allowing them to be modelled appropriately. It also estimates within-subject variability, in addition to estimating model parameters. The method can handle and model missing outcome data under the assumption that the data are missing at random. The mixed model uses a longitudinal data structure that includes both fixed and random effects, and baseline measurement is usually included as a covariate. Time will be included in the model as an interacting categorical variable to observe any time-varying trends. Cohen’s *d* for the effect of Photovoice will be calculated as the difference between baseline-corrected estimated means divided by the pooled standard deviation. A two-sided *p* < 0.05 indicates statistical significance. In addition, demographic variables, such as age, education, gender, marital status, geographic location (i.e., rural vs. urban residence) and household situation (i.e., living with a single and/or an extended family) will be included in the linear mixed models to test for potential moderating and mediating effects on behavioural intention related to burn prevention and first-aid practices. A stepwise selection of the variables will be conducted to determine which variables to keep in the model. As we add the variables, we will immediately eliminate those that do not reduce the Akaike information criterion (AIC) by using the *stepAIC* R function from the library *MASS*. If two or more independent variables in a model are found to be strongly correlated, a variance inflation estimate of less than 5 will be used to determine whether collinearity is present. If the relationship is found to be non-linear, attempts will be made to model the outcome data via the use of splines or polynomials in the *nlme* package in R. The normality of residuals will be assessed graphically using histograms and Q-Q plots. Detailed statistical analyses following Good Clinical Practice: Consolidated Guidelines ICH E9 (52) and Medical Research Council guidelines for developing complex interventions (53) will be described in the statistical analysis plan, which will be finalised before the data lock stage.

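### The non-randomised exposed v non-exposed comparison leaves baseline information-seeking and literacy out of its named covariates and has no rule that controls confounding

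*Protocol article*

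**What the plan says.** Section 2.1 describes a cohort: "This study is a cohort study with three measurement points conducted at 6- to 12-month intervals". It evaluates the campaign on KAP indicators, "as well as psychological variables and health information-seeking variables, among the following groups". The campaign groups are 200 survivors and 100 caregivers exposed to the messages, "burn survivors [*n* = 250] not exposed to campaign messages", and 50 survivors in Photovoice who are also exposed. The abstract gives the purpose: "This design evaluates the impact of the health communication campaign and determines whether Photovoice has any additional effects". Sampling is snowball and purposive (section 2.2.1).

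On the channel, the Introduction states: "The campaign will be disseminated through social media platforms to increase its reach and scalability in Pakistan". It also reports: "There were approximately 71 million social media users in Pakistan as of January 2022, equivalent to 31% of the total population". Section 2.4 adds a website, in-person education sessions, and television and radio publicity.

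On what is known before exposure, sections 2.2 and 2.2.3 place health information-seeking variables in the baseline assessment. Literacy is established at consent and decides the questionnaire mode: "If they are literate, as determined during the informed consent process, they will receive a text message with a Qualtrics questionnaire link". Participants who cannot read are telephoned instead.

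On the model, section 4 names "demographic variables, such as age, education, gender, marital status, geographic location (i.e., rural vs. urban residence) and household situation". Their stated role is to test moderation and mediation of behavioural intention. They go through stepwise selection, and any that does not reduce the AIC is removed. Section 4 also says that the baseline measurement is, as a rule, a covariate. Neither information-seeking nor literacy is named for the quantitative model; health literacy appears only among the group differences for the qualitative analysis.

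**The concern.** Without randomisation, the claim about campaign impact rests on the analysis making exposed and non-exposed survivors comparable. Those who read, go online and look for health information are plausibly more likely to meet a social media campaign. They are also plausibly more likely to learn about burns from other sources during follow-up. Such a trait raises both the chance of exposure and the later KAP score, so part of an apparent campaign effect could be prior habit.

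The baseline KAP score corrects for different starting levels. It does not correct for different learning after baseline. Literacy has a second route to the outcome, because it decides whether KAP is answered through a link or by telephone.

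What is fixed badly is the role and the retention rule of the covariates. Testing a variable as a moderator or mediator is not adjusting for it as a confounder. A rule that keeps variables only for predicting the outcome ignores how strongly they predict exposure.

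**Working it through.** **The plan's own figures.** The sample size in section 2.2.5.10 reproduces as a one-sample test of 63% against 70%, two-sided 5%, with the variance taken at 70%: N = (1.960 + 1.372)² × 0.70 × 0.30 / 0.07² = 476. Power at 478 is 91.6%, against the stated 91.5%. Then 478 / 0.80 = 597.5, rounded up to 598 and stated as 600. This is a before-after calculation, so it says nothing about the between-group contrast. The social media share is also consistent: 71 / 225 million = 31.6%.

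**Bias from an omitted trait.** From the documents: 200 exposed and 250 non-exposed survivors and 20% dropout, which leaves 160 and 200 if dropout is equal across groups. Everything else is assumed: no true campaign effect, a baseline-to-follow-up correlation of 0.5, and a binary trait (for example, being a social media user) that adds g SD to the follow-up score beyond what baseline explains.

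- SE of the group difference = √(1 − 0.5²) × √(1/160 + 1/200) = 0.866 × 0.106 = 0.092 SD.
- Bias = g × (trait prevalence in exposed − prevalence in non-exposed).
- Rejection rate of the 5% test = P(|Z + bias/SE| > 1.96).

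| g | Prevalence, exposed v non-exposed | Bias (SD) | Rejection rate |
|---|---|---|---|
| 0.1 | 50% v 30% | 0.02 | 5.5% |
| 0.2 | 70% v 30% | 0.08 | 14% |
| 0.2 | 90% v 20% | 0.14 | 33% |

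A second set, without dropout (200 v 250) and with correlation 0 to 0.5, gives: 55% v 45% with g = 0.2, bias 0.02 SD, about 6%; 60% v 40% with g = 0.3, 0.06 SD, 10% to 11%; 70% v 30% with g = 0.5, 0.20 SD, 56% to 68%. No case allows for what education, residence or other retained covariates would absorb, so these are upper figures for their inputs.

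**What the AIC rule does to such a trait.** AIC = −2 log L + 2k, so a one-parameter covariate stays only if it raises 2 log L by more than 2, roughly |z| > 1.414. With group in the model, SE(g) = 0.866 / √V, where V = 160 p₁(1 − p₁) + 200 p₀(1 − p₀). The chance of removal is P(|Z + g/SE(g)| < 1.414).

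| Case | V | SE(g) | g/SE(g) | Chance removed |
|---|---|---|---|---|
| 0.1; 50% v 30% | 82.0 | 0.096 | 1.05 | 64% |
| 0.2; 70% v 30% | 75.6 | 0.100 | 2.01 | 28% |
| 0.2; 90% v 20% | 46.4 | 0.127 | 1.57 | 44% |

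At g = 0.2, the trait is dropped more often in the more unbalanced case (44%) than in the less unbalanced one (28%), although its bias there is larger. Adding the variables to the candidate list would therefore not be enough; they must be exempt from selection.

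**The case against.** The strongest reply is that this is detail for the statistical analysis plan. The article's list of variables is open-ended, section 4 defers detailed analyses to that plan, and nothing excludes information-seeking or literacy. The demographic sentence concerns moderation of behavioural intention, so it may never have been meant as the adjustment set for the KAP contrast. This stands as far as the variable list goes. It does not rescue the stated purpose and removal rule, which a variable added to that list would inherit.

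Education and rural or urban residence are partial proxies for literacy and online access, and the baseline score is normally included. These would absorb part of the bias if retained, so it would be wrong to say that the plan adjusts for nothing relevant.

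Three stronger readings are tempting and are not supported.

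- A reader might infer that the comparison is biased in the campaign's favour as a matter of fact. The documents do not say how survivors come to be exposed. Section 2.2.4.1 refers to assignment to a group, section 2.3.1.1 to categorising participants, and the two figures are not available. In-person sessions and mass media also reach people who do not read or use social media. The 31% is a national background figure, not one for these survivors.
- A reader might infer that the needed variables are already in hand. Section 2.2 refers to Table 1 for the full variable list, yet neither Table 1 nor section 2.2.5 names an information-seeking instrument. Social media use is not stated as measured. Literacy is determined, but not said to be recorded for analysis, and it is reading literacy, not health literacy.
- A reader might extend the argument to Photovoice v exposed. Both of those groups receive the campaign messages, so selection into seeing them does not explain a difference. Selection into Photovoice is a separate matter needing its own rationale.

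**Conclusion.** The point holds as a plausible, unquantified risk of confounding in the exposed v non-exposed comparison of survivors on KAP, with a direction that probably favours the campaign. It rests on three features of the article: no randomisation is described; exposure comes largely through social media; and the named covariates are demographic, serve moderation and mediation, and are removed on AIC.

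The size cannot be derived from the documents. The illustrations run from negligible (0.02 SD, 5.5% to 6% rejection under no effect) to serious (0.14 SD and 33%, or 0.20 SD and 56% to 68%). Every trait prevalence, gain and correlation behind them is assumed, and the existence of the bias further assumes that information habits influence who is exposed. The change is worth making because it costs almost nothing and concerns variables that the protocol says it obtains before exposure.

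**What to change.** In section 4, state that the exposed v non-exposed models include, as fixed covariates exempt from AIC selection:

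- the baseline score of the outcome, without the present hedge;
- the baseline health information-seeking measure;
- literacy as determined at consent.

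Use baseline values only, because later information-seeking may itself be changed by the campaign. Tabulate these variables by group so that readers can see the imbalance. Keep the moderation and mediation analyses as a separate step.

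Name the information-seeking measure in Table 1 or section 2.2.5, and record literacy as an analysis variable. If the measure does not cover social media use, one baseline item would supply it. Give the Photovoice v exposed comparison its own covariate rationale.

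The cost is some wording, a few degrees of freedom and at most that one item. No stated sample size changes. Unmeasured differences remain after adjustment, so the result should still be reported as a non-randomised comparison.

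### A third of the exposure group, and nobody in the other two groups, is a caregiver, so a KAP comparison by the groups as defined carries one third of any caregiver-survivor difference

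*Protocol article*

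**What the plan says.** The Research design section (2.1) and the abstract define three groups:

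- exposure: "burn survivors [*n* = 200] and caregivers [*n* = 100] exposed to campaign messages";
- non-exposure: "the non-exposure group (i.e., burn survivors [*n* = 250] not exposed to campaign messages";
- Photovoice: "burn survivors [*n* = 50] who participate in Photovoice and are exposed to the campaign messages".

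The abstract states that "The primary outcomes are knowledge, attitudes and practices regarding burn injuries", and says of the grouping that "This design evaluates the impact of the health communication campaign" and shows whether Photovoice adds anything. Section 2.1 likewise says that impact will be evaluated among these groups.

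Table 1 marks KAP for survivors and family members. Each psychological scale is marked for survivors only.

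The Data analysis plan (section 4) sets out a linear mixed model on N = 600. Its stated aim is "To compare changes in self-reported outcomes within groups across two time points", and it remarks that "baseline measurement is usually included as a covariate". It adds a Cohen's d for Photovoice, taken as a difference in baseline-corrected means. The variables it names are demographic; survivor or caregiver status is not among the examples. No section says which participants enter an exposed v non-exposed contrast on KAP.

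**The concern.** Caregivers and survivors are different populations. The caregiver criteria (2.2.4.2) admit relatives of people who died of their burns, and one sample practice item in the KAP scale asks what the respondent has done in the event of a burn. The two types could plausibly differ in KAP level, in KAP change, or in both, for reasons unrelated to the campaign.

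Because caregivers are present in one group only, part of such a difference would be counted as campaign effect, or subtracted from it, on the primary outcome. The direction is unknown, so the bias could create an apparent effect or hide a real one. A comparison of Photovoice with the exposure group on KAP is affected in the same way with the opposite sign, although the stated Photovoice objective concerns burn survivors.

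**Working it through.** **Inputs from the protocol article.** Group sizes are from section 2.1: 200 survivors + 100 caregivers exposed, 250 survivors non-exposed, 50 survivors in Photovoice. The 20% dropout is from the sample size paragraph that closes section 2.2.5. The two-sided 5% level is from section 4.

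**The plan's own total.** 200 + 100 + 250 + 50 = 600. Inflating the stated 478 for dropout gives 478/(1 − 0.20) = 597.5, or 598, which agrees with 600 after rounding. That calculation is for baseline v follow-up, not for exposed v non-exposed.

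**Share of caregivers.**

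- Exposure: 100/300 = 33.3%.
- Non-exposure: 0/250 = 0%.
- Photovoice: 0/50 = 0%.
- If Photovoice were pooled with exposure: 100/350 = 28.6%.

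**Bias.** Let g be the caregiver-survivor difference that is unrelated to the campaign, in SD of the variable analysed. For an unadjusted follow-up comparison, g is a difference in level. For a change or baseline-adjusted analysis, it is a difference in change. The pooled contrast is then biased by g × (100/300 − 0/250) = g/3.

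**False-positive rate.** With 20% dropout, 300 v 250 becomes 240 v 200, and SE = √(1/240 + 1/200) = 0.0957 SD. With no campaign effect, the rejection rate is 1 − Φ(1.96 − bias/SE) + Φ(−1.96 − bias/SE). The documents give no value for g, so a range is assumed:

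| Assumed g (SD) | Bias g/3 (SD) | 240 v 200 | 300 v 250, no dropout |
|---|---|---|---|
| 0.1 | 0.033 | 6.4% | 6.8% |
| 0.2 | 0.067 | 10.7% | 12.2% |
| 0.3 | 0.100 | 18.1% | 21.5% |
| 0.5 | 0.167 | 41.3% | 49.5% |

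**Precision of a survivors-only contrast.** Minimum detectable difference at 80% power = (1.96 + 0.8416) × √(1/n₁ + 1/n₂):

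- Pooled, 300 v 250: 2.8016 × 0.0856 = 0.240 SD.
- Survivors only, 200 v 250: 2.8016 × 0.0949 = 0.266 SD.
- Pooled after dropout, 240 v 200: 2.8016 × 0.0957 = 0.268 SD.
- Survivors only after dropout, 160 v 200: 2.8016 × 0.1061 = 0.297 SD.

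**N for the psychological scales.** Table 1 gives these to survivors only: 200 + 250 + 50 = 500, whereas section 4 names a single sample of 600.

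**The case against.** The strongest reply is that no section states a pooled 300 v 250 test. Section 4 speaks of change within groups, the sample size rests on baseline v follow-up, and the one effect size named is for Photovoice. Change within a group is not confounded by how that group differs in make-up from another. The article also defers detail to a statistical analysis plan, and its covariate list is open-ended and serves to examine moderation and mediation. The absence of a participant-type term from that list therefore proves little.

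Much of this stands. The false-positive rates belong to an analysis that the article implies but does not specify. It does not dispose of the point, because the group definitions are fixed in the article and the article says the campaign is evaluated among those groups. Within-group change alone cannot compare exposed with non-exposed.

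A reader might go further and infer that exposure and participant type are inseparable, so that no adjustment could help. The documents do not support this. There are survivors on both sides, 200 and 250. In a model with group-by-time and participant-type-by-time terms, the caregiver term absorbs the caregivers' own mean, and the exposure coefficient comes from survivors, apart from any covariates shared across types.

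A reader might also infer that caregivers are paired with enrolled survivors, so that the model ignores family clustering. Recruitment of survivors and family members at the same centres makes this possible, but nothing says that linked pairs are enrolled.

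On the count of 600, the article does say that not everyone receives the same questionnaires, and Table 1 shows who does. This is a matter of wording only.

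**Conclusion.** The point holds in a limited form. On KAP, a comparison by the groups as defined mixes campaign exposure with participant type and is biased by one third of whatever caregiver-survivor difference exists. Nothing in the article restricts the contrast or adjusts for type.

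The factor of one third follows from the stated group sizes and assumes equal dropout in the two types. The rest of the size is conditional. For assumed differences of 0.1 to 0.5 SD, the bias is 0.03 to 0.17 SD. The false-positive rate after dropout runs from about 6% to 41%, under a normal approximation to a simple two-group comparison. None of these rates should be read as the expected error rate of the study, since the true difference is not given. Baseline adjustment would reduce the problem, but would not remove it if the two types change differently.

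The survivor contrast is estimable within the present design. What the design cannot supply is a concurrent comparator for the campaign effect in caregivers.

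**What to change.** State in section 4, and carry into the statistical analysis plan before it is finalised, that:

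1. between-group KAP contrasts are in survivors only: 200 exposed v 250 non-exposed, and 50 Photovoice v 200 exposed. Equivalently, the model includes a participant-type-by-time term and the survivor contrast is the one reported;
2. the 100 caregivers are reported separately, as an uncontrolled before-after description of KAP with no causal claim;
3. the analysis N is 500 for the survivor-only psychological scales.

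The change is to wording only and needs no new recruitment or data. The cost is that the exposed arm of the KAP contrast falls from 300 to 200, with the modest loss of precision shown above (0.297 v 0.268 SD after dropout), and that the caregiver results stay descriptive.
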